## Discussion

This study protocol presents the design of an open label clinical trial evaluating the efficacy of baclofen to prevent relapse, reduce craving and anxiety, and to assess the safety profile of baclofen in GHB dependent patients. To date, there are no reports on the potential of baclofen to prevent relapse in GHB dependent patients. We expect that baclofen will increase abstinence rates, reduce craving and will be well tolerated. In addition, baclofen may improve psychiatric symptoms such as anxiety and depression, as suggested in several clinical trials in alcohol-dependent individuals [29,30,46].

Several risks of baclofen use are taken into account in the current study. In patients with neuropsychiatric disorders, such as schizophrenia, severe depression, mania, Parkinson’s disease and cerebrovascular diseases, exacerbations of these conditions may occur, when the dose of baclofen is rapidly increased. It may lower the threshold for seizures in epileptic patients [42]. To limit these risks in the current trial, baclofen will be uploaded gradually, over a period of minimally 10 days. Moreover, patients previously diagnosed with any of the mentioned diseases will be excluded from the study.

Abrupt discontinuation of baclofen, when used for several months, can be associated with a withdrawal syndrome which resembles benzodiazepine and alcohol withdrawal. Several symptoms are reported such as hallucinations, fever, confusion, delirium, agitation, insomnia, and muscle stiffness and spasms [47]. Therefore, patients will be advised to taper down slowly when discontinuation is needed.

Intoxication with baclofen has been reported in doses above 100 mg [48]. This risk increases if patients combine baclofen with GHB. Intoxication is not expected when baclofen is administered at a low dose (<30 mg per gift), as applied in the current study. Patients will however, be informed repeatedly of this potential risk and the treatment will be discontinued immediately in case of relapse.

The current study does have several limitations. First, the study is not randomized, nor placebo controlled. However, we will compare patients receiving baclofen with a control group matched for gender, age and the pattern of GHB use, in order to control for potential confounding factors. Second, the accompanying treatment as usual (TAU) is not identical in all participating addiction care facilities. This may confound our results. The impact of TAU will be checked with a sensitivity analysis compare patients’ results from the different centers conforming the add-on baclofen effect.

Given these methodological limitations the current study should be considered explorative in nature. Given the currently rather limited information from both preclinical and clinical studies of GHB such an explorative approach seems justified. We would also like to test the GHB substitution effect of baclofen (as a GABA-B agonist) hypothesis. It is important to evaluate of this effect is clinically recognized and obvious for the participants, and may define placebo use as non-beneficial. We need to be able to determine the margins of the required treatment dose. All forgoing justify this setup of an open label trail before a large placebo controlled randomized trial.

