### Study intervention

#### Baclofen intervention

Clinical trials on baclofen for alcohol dependence treatment have used baclofen at a dose of 30 mg ⁄d [29-31] over 30 to 120 days. This is within the low therapeutic range for muscle spasms. However, Garbutt and colleague’s [32] suggested that 30 mg of baclofen per day may be an insufficient dose for some patients to achieve abstinence. Additionally, baclofen effectiveness for GHB dependence could be smaller, since tolerance may occur due to recent abuse of GHB and a possible substitution function (as treatment will be started immediately after detoxification).

Based on these results and the unpublished results of a small dose finding experimental treatment study in our treatment center, where patients reported limited effect of baclofen 30 mg per day, we decided to administrate a dose of 45 mg to a maximal dose of 60 mg per day orally to avoid the risk of (co) intoxication. In this study baclofen will be administrated orally three times daily as usually recommended [22] and started with a total dose of 15 mg per day. During the first 10 days baclofen will be gradually increased with 15 mg per day every 3 days up to the chosen minimum dose of 45 mg, or a maximum dose of 60 mg in case no effect is reported at 45 mg after 2 weeks. This dose will subsequently be maintained for a period of 10 weeks. Successively, baclofen will be tapered off to 0 mg in 2 weeks (see Table 1). Patients will be asked to avoid abrupt termination of baclofen and will be guided by their physician to avoid complications of baclofen withdrawal. Patients who wished to continue the baclofen treatment will be offered an outpatient counselling and medication by their physician for another 3 months.

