**Table 1 Tab1:** **Baclofen dose in mg/week**

**Week**	**1**	**2**	**3**	**4**	**5**	**6**	**7**	**8**	**9**	**10**	**11**	**12**	**13**	**14**	**15**
Doses a day	15–30	45–60	45/60	45/60	45/60	45/60	45/60	45/60	45/60	45/60	45/60	45/60	30–45	15–30	15–0

Compliance will be assessed based on self-report, urine test for GHB, and empty pill counts. The physician will make use of the BRENDA method, a psychosocial program designed to enhance medication and treatment compliance [33,34]. In case of GHB use during baclofen treatment, participants are expected to contact the research physician. In case of relapse, immediate cessation of treatment will be considered to avoid intoxication hazards.

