#### Additional measures

Addiction physicians will be asked to monitor withdrawal symptoms when tapering baclofen, using standard questions. These include a short check of the most reported withdrawal symptoms in the literature [43,44].

We will monitor the use of other substances over the last thirty days (number of days and quantity) using section 1 of the Measurement of Addicts for Triage and Evaluation (MATE) before and after detoxification and at follow up (3 months). The MATE is a Dutch instrument designed as an aid in the diagnosis of clinically relevant patient characteristics in substance use disorders according to the DSM-IV axes [45].

At 6 month period we will also report on the needed period of treatment with baclofen to maintain abstinence by monitoring relapse (Timeline Follow back) and craving assessment (DDQ, VAS) within the intervention group between those who used baclofen for 3 month only and those who choose to continue the treatment further.

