**Table 2 Tab2:** **Time measurements**

**Week**	**0**	**1**	**2**	**3**	**4**	**5**	**6**	**7**	**8**	**9**	**10**	**11**	**12**	**13**	**14**	**15**	**24**
Measurement	**T0**-baseline	**T1**											**T2**				**T3**
Mate section	xx												xx				x
EQ–5D	xx												xx				x
DASS	xx												xx				x
Mini-plus	xx												xx				x
Blood	xx						x						x				
Urine	xx						x						xx				x
Medical consult	2x	2x	2x	x	x			x			x		x	x	x		
Baclofen (mg)	0	15–30	45– 60											30–45	30–15	15–0	0
Baclofen Side effect	x	2x	2x	x	x			x			x		x				
VAS	xx	x	x	x	x			x			x		xx				x
DDQ	xx	x	x	x	x			x			x		xx				x
Baclofen withdrawal checklist														x	x	x	
Timeline follow back													xx				x

xx = baclofen group and control group TAU only.

x = baclofen group.

T0 = end of GHB detoxification.

T1 = start baclofen treatment.

T2 = follow-up TAU only and end of baclofen therapy.

T3 = follow-up baclofen group.

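### The Discussion presents two baclofen safety measures, stopping at relapse and excluding cerebrovascular disease, that the Methods do not deliver as stated

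*Protocol article*

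**What the plan says.** **Relapse.** In the Methods (Baclofen intervention, text below Table 1): "In case of relapse, immediate cessation of treatment will be considered to avoid intoxication hazards". In the Discussion, on the risk of combining baclofen with GHB: "the treatment will be discontinued immediately in case of relapse".

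**Ending baclofen in general.** The Baclofen intervention section says: "Patients will be asked to avoid abrupt termination of baclofen and will be guided by their physician to avoid complications of baclofen withdrawal". The Discussion warns that "Abrupt discontinuation of baclofen, when used for several months, can be associated with a withdrawal syndrome", and concludes that "patients will be advised to taper down slowly when discontinuation is needed".

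**Watching for withdrawal.** Under Additional measures: "Addiction physicians will be asked to monitor withdrawal symptoms when tapering baclofen, using standard questions". In Table 2 the row "Baclofen withdrawal checklist" is marked in weeks 13, 14 and 15 only.

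**Exclusions.** The In- and exclusion criteria rule out severe mood disorder and psychotic disorder if current, seizure disorder and Parkinson's disease. A general clause also rules out any current physical or psychiatric safety concern. The Discussion names schizophrenia, severe depression, mania, Parkinson's disease, cerebrovascular disease and epilepsy as conditions in which baclofen carries risk. It states that anyone previously diagnosed with one of them will be excluded.

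**The concern.** The Discussion offers the stop at relapse as protection against intoxication, and the exclusions (with gradual titration) as protection against worsening of existing disease. Both are worded as settled. A reader who turns to the Methods finds a stop that is optional and an exclusion list without one of the named diseases. The two texts therefore give different answers for the same patient, and the article does not say which governs.

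Patient safety is at stake, in two ways. A patient who relapses may be kept on baclofen in line with the Methods but against the Discussion. A patient with past cerebrovascular disease may be enrolled in line with the listed criteria although the Discussion says this cannot happen. If baclofen is stopped at once, the withdrawal checklist that the study already has is not scheduled for that moment.

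**Working it through.** No figure in the plan rests on these rules, so the check sets the texts side by side.

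**1. Relapse rule.**

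| Physician's action at relapse | Methods (stop to be considered) | Discussion (stop is certain) |
|---|---|---|
| Stops at once | allowed | required |
| Tapers under supervision | allowed | breach |
| Continues | allowed | breach |

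Only the first action satisfies both texts.

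**2. Size of the dose step.** Table 1 gives 45 or 60 mg/day in weeks 3 to 12, then 30–45, 15–30 and 15–0 mg/day in weeks 13, 14 and 15. The planned ending thus passes through three weekly dose ranges. An immediate stop in weeks 3 to 12 is a single step from 45 or 60 mg/day to 0.

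**3. Checklist coverage.** Additional measures ties withdrawal monitoring to tapering, so its wording covers a taper begun early. It does not cover a stop without a taper, and Table 2 has no checklist before week 13.

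**4. When this matters most.** The Discussion links withdrawal to several months of use. At 4.35 weeks per month, the end of week 12 is 12 / 4.35 = 2.8 months. The article also provides that "Patients who wished to continue the baclofen treatment will be offered an outpatient counselling and medication by their physician for another 3 months", which brings exposure to about 2.8 + 3 = 5.8 months. The gap therefore matters mainly for relapse late in the 12 weeks or during the optional extension.

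**5. Exclusions.**

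| Condition named in the Discussion | In the Methods criteria |
|---|---|
| Parkinson's disease | named |
| Epilepsy | named, as seizure disorder |
| Schizophrenia | named, if current |
| Severe depression | named, if current |
| Mania | covered as bipolar disorder, if current |
| Cerebrovascular disease | not named |

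The last row differs however *previously diagnosed* is read. The three rows limited to current disorder differ only if the term includes past, remitted illness.

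**6. Effect on the statistics.** The sample size uses 70% against 36% abstinent and 25% drop-out. None of these inputs depends on either rule.

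**The case against.** The strongest reply is that the Methods are the operative text and the Discussion only retells them, in an article that condenses a fuller protocol. Sites presumably work from that protocol, so a reader might infer from the article that the six facilities will in fact treat like patients differently. The documents do not show this. What stands is that the article gives two rules for the same event and does not say which one applies.

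It is also tempting to say that stopping at once contradicts the advice to taper slowly. That goes too far. A general rule on ending treatment can coexist with a specific rule for an intoxication hazard. The promised guidance by the physician is not limited to the scheduled taper, and participants who use GHB are expected to contact the research physician. These partly cover an early stop. What remains is that no withdrawal checklist is scheduled for it.

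On exclusions, a reader might count four of the six named conditions as inconsistent. That depends on taking *previously diagnosed* to include illness that has resolved. The Discussion is concerned with exacerbation of these conditions, which fits known, existing disease equally well; on that reading only cerebrovascular disease differs. The article does mention that the MINI-plus separates current from lifetime disorder, but it does so in describing an outcome instrument, which does not settle eligibility. The general safety clause is mandatory and is backed by medical screening, so a current cerebrovascular problem would probably be caught. A past event might not be.

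**Conclusion.** The point holds as a minor inconsistency in safety wording. The relapse rule is firm in the Discussion and discretionary in the Methods. Cerebrovascular disease is excluded in the Discussion and not named in the Methods. An immediate stop has no scheduled withdrawal checklist. The status of past, remitted mood or psychotic disorder is ambiguous rather than contradictory.

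The number of patients affected cannot be derived. A reader might take the expected 70% abstinence to imply that 30% of 40, or 12 patients, would meet the relapse rule. The documents do not support that step: abstinence in the sample size section need not match the relapse definition under Statistical analyses (at least 3 uses per day on 2 successive days), and the 40 includes an allowance for drop-out.

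Nor do the documents show an effect on the primary comparison, and none is claimed. Whether to stop at once or to taper is a clinical trade-off between intoxication and withdrawal, and this review takes no side on it. The conclusion assumes only that both texts describe the same trial and that no other text shown ranks one above the other.

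**What to change.** 1. State the same relapse rule under Baclofen intervention and in the Discussion. The responsible clinicians decide whether it is an immediate stop or a supervised taper. If it is an immediate stop, say that this is the exception to the slow taper.
2. Add under Additional measures that the baclofen withdrawal checklist is also completed whenever baclofen is stopped early.
3. Add cerebrovascular disease to the In- and exclusion criteria.
4. In the Discussion, replace *previously diagnosed* by the criteria in the Methods. If past mood or psychotic disorder is meant to exclude, say so in the Methods instead.

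The cost is a short clarification to the six facilities and the ethics committee, a few extra checklist completions and slightly narrower eligibility. Eligibility narrows further only if past disorder is made an exclusion; the article gives no share of patients from which to estimate by how much. Sample size and tests stay as they are.

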### Implications for practice

If our study confirms the potential of baclofen to reduce relapse and craving without serious adverse events in GHB-dependent patients, this warrants large scale randomized controlled trials in order to draw more firm conclusions. If baclofen showed to have beneficial effects on psychiatric symptoms in these patients, baclofen might be specific interest for the treatment of those GHB dependent patients with co-morbid high levels of anxiety and depression.
